## Abstract

**Introduction:** Rheumatoid arthritis (RA) is a chronic autoimmune disease affecting females more than males. Clinical symptoms, disease activity and comorbidities are more severe in females. Moreover, the choice of treatment for females is limited during childbearing age due to the side effects of current drugs. Therefore, developing novel and safer drugs for females is urgently needed. Kunbixiao granules (KBXG), a Chinese medicine formula, has been applied to treat female RA patients in our center as a complementary therapy. However, there is insufficient evidence for its effect. Therefore, we aim to conduct a randomized, controlled, double-blind clinical trial to confirm the efficacy and safety of KBXG for the treatment of female RA.

**Methods:** This study is a single-center, double-blind, randomized, parallel group, placebo-controlled clinical trial. A total of 90 female RA patients with Disease Activity Score for 28 joints (DAS28) > 3.2 will be enrolled. They will be randomly assigned to receive either KBXG or placebo for 12 weeks. The change in DAS28 based on C-reactive protein (DAS28-CRP) and the Clinical Disease Activity Index (CDAI) are the primary outcomes. The secondary outcomes include a rate of achieving 20%, 50% and 70% improvement in the American College Rheumatology criteria (ACR20, ACR50, ACR70), TCM syndrome score, visual analogue scale (VAS), average hands grip strength, the consumption of concomitant medication, Hospital Anxiety and Depression Scale (HADS), lumbar spine bone mineral density (L-BMD) and 7-joint ultrasound score (US7). Any adverse events will also be recorded.

**Discussion:** This trial will provide evidence of KBXG in reducing disease activity, and improving clinical symptoms and quality of life of female RA patients. The long-term effects of KBXG on female RA patients still needs a further follow-up.

## Introduction

Rheumatoid arthritis (RA) is a chronic, progressive and autoimmune disease characterized by tissue damage, functional disorder, serious disability and premature mortality (Otón and Carmona, 2019; Firestein et al., 2020). A recent epidemiologic study showed RA affected about 1% of the world’s population (McInnes and Schett, 2017). The morbidity of RA is highest at the age of 50, with female patients as the main population (van der Woude and van der Helm-van Mil, 2018). Women are three to four times more prone to develop the disease than men, with data demonstrating a progressive increase in the incidence of RA in females during the last decade (Myasoedova et al., 2020). Meanwhile, RA seems to be more severe in women with higher disease activity, lower rates of remission and drug survival (Favalli et al., 2019; Maynard et al., 2020). More frequent comorbidities in female RA, such as depression, osteoporosis and fibromyalgia, also may impact treatment choice and outcomes (Albrecht, 2014).

At present, the treatments of RA mainly include non-steroidal anti-inflammatory drugs (NSAIDs), glucocorticoids, conventional synthetic disease-modifying anti-rheumatic drugs (csDMARDs) and biologic disease-modifying anti-rheumatic drugs (bDMARDs) (Singh et al., 2016). These drugs have multiple side effects, such as hepatorenal damage, peptic ulcer bleeding, cardiovascular complications, infection, and risk of carcinoma (Zamanpoor, 2019). Moreover, the use of these conventional drugs for treating female RA may be conditioned during childbearing age, pregnancy, and lactation (Ngian et al., 2016; Abbasi et al., 2019). Thus, it is necessary for exploring novel and safer therapeutic strategies for female patients of RA.

Traditional Chinese Medicine (TCM) has shown advantages in the treatment of RA. Chinese medicine formula monotherapy or combined with Western medicine had better performance on improving clinical symptoms, preventing the disease progression, reducing serum rheumatoid factor and anti-cyclic citrullinated peptide antibodies, and improving the bone mineral density of RA than Western medicine monotherapy (Cai, et al., 2018; Tang, et al., 2021; Zhang et al., 2022). But to date, there is no TCM clinical trial for RA in women. According to TCM theory, the Qi-blood deficiency and the toxin-heat blocking joints are the most common pathogenesis for female RA. KBXG, as a Chinese medicine formula, is composed of two traditional well-known formulas Simiao Yong’an decoction and Siwu decoction. It has been used in treating female RA patients in our center for decades. We have examined the efficacy of KBXG on collagen-induced arthritis (CIA) rats. The results showed that KBXG demonstrated favourable effect on inhibiting inflammation, synovial hyperplasia and joint destruction of CIA rats. (Ma et al., 2022). Additionally, our previous clinical study confirmed that KBXG could significantly improve clinical symptoms and reduce disease activity without any adverse events (AEs) (Niu, 2020). Nevertheless, there is no reliable evidence from evidence-based trials to popularize its use for treating female RA. Therefore, we conduct a well-designed, randomized double-blind controlled clinical trial to confirm the efficacy and safety of KBXG for the treatment of female RA.

## Methods

### Trial design

This is a single-center, randomized, double-blind, parallel group, placebo-controlled clinical trial. The trial will be conducted in the Xiyuan Hospital of China Academy of Chinese Medical Sciences. A total of 90 eligible female participants will be randomized into the experimental group (KBXG) or the control group (placebo) with a 1:1 ratio. Two groups will continue their original treatment regimen during the trial. The duration of the intervention is 12 weeks, and follow-up is 12 weeks. Study visits will take place at baseline and at 4, 8, 12, 24 weeks. Every patient will be asked to visit within 3 days of the given time point. All participants will be required to sign the written informed consent before randomization. This protocol was compiled in line with the Standard Protocol Items: Recommendations for Interventional Trials (SPIRIT) Guidelines (Chan et al., 2013), which is presented in the Supplementary Material S1. The flowchart of this trial is presented in Figure 1.

**FIGURE 1 F1:**
[figure not shown]
Study flowchart.

### Participants

90 female participants will be recruited at Xiyuan Hospital *via* putting up posters in the hospital areas. A rheumatologist will be responsible for screening participants and assessing whether they meet with the inclusion criteria. A research assistant will provide the participants with the informed consent form.

#### Diagnostic criteria

##### Diagnostic criteria for RA

In accordance with the classification criteria of RA proposed by ACR and European League against Rheumatism (EULAR) in 2010, participants with a score of 6 or above will be diagnosed with RA (Kay and Upchurch, 2012).

##### Diagnostic criteria for active RA

DAS28 > 3.2. DAS28, a commonly accepted measure for disease activity (van Riel and Renskers, 2016). According to EULAR diagnostic criteria for RA activity, 2.6 < DAS28 ≤ 3.2, 3.2 < DAS28 ≤ 5.1, and DAS28 > 5.1 represent low, moderate, and high disease activity, respectively (Fransen et al., 2004). DAS28 > 3.2 means the disease is active.

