##### Diagnostic criteria for TCM syndrome differentiation

Patients have at least two of the primary symptoms, or one of the primary symptoms and more than two of the secondary symptoms, indispensable tongue and pulse listed in the following to be diagnosed with the Qi-blood deficiency, toxin-heat blocking joints syndrome.1). Primary signs and symptoms: joint pain; joint swelling; morning stiffness; activity limitation.2). Secondary signs and symptoms: redness of joint; local joint fever; fatigue; thirsty upset; dry stools and yellow urine.3). Tongue and pulse: red tongue with yellow greasy or thin yellow fur, rapid and slippery pulse or soft pulse.

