#### Inclusion criteria

Participants meeting the following criteria will be included:1) Females aged 18–65 years old.2) Patients who meet the diagnostic criteria for RA, meet the diagnostic criteria for active RA, and meet the Qi-blood deficiency, toxin-heat blocking joints syndrome.3) A duration of RA for at least 3 months prior to enrollment.4) Patients who take only one kind of csDMARDs (methotrexate at a dose of 15–20 mg per week at least or leflunomide at a dose of 20 mg per day) were given a stable dose for at least 12 weeks before screening and remained at the same dose for the rest of the treatment.5) Patients who volunteer to participate in the trial and sign the informed consent form.

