### Outcomes and measurements

#### Primary outcome

The primary outcomes are the change in DAS28-CRP and CDAI at every visit.

The DAS28-CRP is widely used as an indicator of RA disease activity and response to treatment, and clinical trials have used DAS28 to assess treatment effect (Gardiner et al., 2005; Jain et al., 2021; Zhang et al., 2022). A change of ≥1.2 score is considered clinically significant difference (Van Gestel et al., 1998). The DAS28-CRP is calculated as DAS28-CRP = 0.56*sqrt (TJC28) + 0.28*sqrt (SJC28) + 0.36*ln (CRP+1) + 0.014*VAS +0.96 (van Riel, 2014).

The CDAI is calculated as CDAI = TJC28 + SJC28 + overall disease activity on a 0–10 VAS completed by the patient + overall disease activity on a 0–10 VAS completed by the physician (Aletaha et al., 2005). High disease activity is defined as a CDAI >22, moderate activity as a CDAI >10 and ≤22, low activity as a CDAI >2.8 and ≤10, and remission as a CDAI ≤2.8.

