#### Secondary outcomes

Secondary outcomes are the following:1) The rate of achieving ACR20, ACR50, ACR70 (Felson and LaValley, 2014). Measurement will be performed at every visit. Briefly, ACR20/ACR50/ACR70 is defined as a more than 20%/50%/70% improvement respectively in both tender joint count (TJC) and swollen joint count (SJC). Patients should simultaneously have a more than 20%/50%/70% improvement respectively in at least 3 items as follow: patient’s assessment of pain on a VAS, patient’s global assessment of disease activity, physician’s global assessment of disease activity, HAQ-DI and CRP level.2) Changes in TCM syndrome score. It will be evaluated based on the grading scales of RA symptoms required in the Guiding Principles of Clinical Research of New Chinese Medicine Treating RA (2002 Edition) issued by the National Medical Products Administration of China at every visit. The scores and details are presented in the Supplementary Material S4.3) Changes in VAS. Pain will be evaluated using a VAS at every visit according to a former study (Faiz, 2014).4) Changes in average hands grip strength. Measurement will be performed at every visit. The Jamar dynamometer is used to assess the hand grip strength (Higgins et al., 2018). For each strength test, three times of measurements should be done for each hand, and the mean score of both hands is recorded.5) Changes in HADS. Anxiety and depression will be evaluated at every visit according to a former study (Herrero et al., 2003).6) Changes in lumbar spine bone mineral density (L-BMD) to assess osteoporosis. Measurement will be performed at baseline and week 24.7) Changes in 7-joint ultrasound score (US7). Measurement will be performed at baseline and week 12, 24. It determines the severity of synovitis, synovial hyperplasia and bone erosion of 7 joints through color Doppler ultrasound semi-quantitative assessment (Backhaus et al., 2009). The scores and details are presented in the Supplementary Material S5.8) Consumption of concomitant medications. We will record any changes in the dose of NSAIDs or oral corticosteroids in the case report form (CRF). The drug name, total daily dose, and single dose will be record at every visit.

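### Entry sets no minimum tender or swollen joint count, so patients can be enrolled whose ACR20/50/70 response cannot be met or evaluated

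*Protocol article*

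**What the plan says.** **Entry.** Under Diagnostic criteria for active RA, the rule is "DAS28 > 3.2 means the disease is active". Inclusion criterion 2 applies it: patients must satisfy the RA diagnosis, "meet the diagnostic criteria for active RA, and meet the Qi-blood deficiency, toxin-heat blocking joints syndrome". The RA diagnosis is given only as a total: "participants with a score of 6 or above will be diagnosed with RA". The syndrome rule reads "Patients have at least two of the primary symptoms, or one of the primary symptoms and more than two of the secondary symptoms", together with tongue and pulse signs, and draws on this list: "Primary signs and symptoms: joint pain; joint swelling; morning stiffness; activity limitation". Neither the inclusion nor the exclusion list contains a joint-count minimum.

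**Score.** The Primary outcome section gives "DAS28-CRP = 0.56*sqrt (TJC28) + 0.28*sqrt (SJC28) + 0.36*ln (CRP+1) + 0.014*VAS +0.96". The entry criterion does not say whether its DAS28 uses CRP or ESR, but Table 2 schedules DAS28-CRP at the enrolment visit, so that formula is used here.

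**Outcome.** ACR20/50/70 is the first of eight listed secondary outcomes. Its joint component asks for more than the stated percentage "improvement respectively in both tender joint count (TJC) and swollen joint count (SJC"). At least three of five further items must improve by the same margin.

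**The concern.** A composite score can be high because of one or two of its parts. A percentage improvement in both joint counts needs each count to start above zero. If the entry rule does not secure that, the trial can enrol women whose ACR response is settled, or has no value, before the first dose.

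Counted as non-responders, such patients pull down both arms' ACR rates and the difference between them. Left out, they reduce the number analysed. Either way the ACR comparison loses sensitivity.

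**Working it through.** There is no stated figure to reproduce on this point. The check puts the article's formula to the article's threshold and then reads the ACR rule against the result.

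**Inputs.** Formula: Primary outcome. Threshold 3.2: Diagnostic criteria for active RA. ACR rule: Secondary outcomes. 45 per arm: Sample size. Assumed, because not stated: CRP in mg/L and VAS on 0-100.

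**Step 1: can the threshold be passed with a zero count?**

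TJC 6, SJC 0, CRP 5, VAS 50:
0.56 × √6 + 0.28 × √0 + 0.36 × ln 6 + 0.014 × 50 + 0.96 = 1.372 + 0 + 0.645 + 0.700 + 0.960 = **3.68**.

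TJC 0, SJC 6, CRP 20, VAS 50:
0 + 0.686 + 1.096 + 0.700 + 0.960 = **3.44**.

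Further cases:

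| TJC | SJC | CRP | VAS | DAS28-CRP | Above 3.2? |
|---|---|---|---|---|---|
| 1 | 0 | 10 | 60 | 3.22 | yes |
| 2 | 0 | 10 | 50 | 3.32 | yes |
| 10 | 0 | 10 | 60 | 4.43 | yes |
| 0 | 2 | 10 | 70 | 3.199 | no |
| 0 | 4 | 10 | 60 | 3.22 | yes |
| 0 | 0 | 20 | 90 | 3.32 | yes |
| 1 | 1 | 10 | 50 | 3.36 | yes |

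Over a grid of CRP 3, 5, 10 and 20 and VAS 30 to 70 in steps of 10, a patient with no swollen joint needs 1 to 6 tender joints to qualify. A patient with no tender joint needs 1 to 23 swollen joints. Zero swollen joints is therefore the realistic route. Zero tender joints needs more swelling or a higher CRP or VAS, and both counts at zero needs a high CRP and VAS together.

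**Step 2: does another criterion close the gap?** No. Two primary symptoms satisfy the syndrome rule, given the tongue and pulse signs. Pain with morning stiffness does so without swelling, and swelling with morning stiffness does so without pain. The RA diagnosis, as stated, is a total score with no current joint count.

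**Step 3: the ACR rule at low baseline counts.** Percentage improvement = (baseline − follow-up) / baseline.
- Baseline 0: the denominator is 0, so the condition cannot be evaluated and no improvement is possible.
- Baseline 1: only a fall from 1 to 0 (100%) counts, so the joint component is the same for ACR20, ACR50 and ACR70.
- Baseline 2: a fall from 2 to 1 is exactly 50%, which does not exceed 50%, so ACR50 and ACR70 need the same change.

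**Step 4: effect on the ACR comparison.** Let f be the share with a zero count, counted as non-responders, and let p₁ and p₂ be the rates among the rest. The observed rates are p₁(1−f) and p₂(1−f), and the difference is (p₁−p₂)(1−f).

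Purely as an illustration, take ACR20 rates of 50% and 25% (assumed, not in the documents), 45 per arm and two-sided 0.05. Power = Φ[(d − 1.96 × s₀)/s₁], where d is the difference, s₀ its standard error with pooled variance and s₁ its standard error with separate variances.

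| f | Rates | Difference (points) | Power |
|---|---|---|---|
| 0 | 50% v 25% | 25.0 | 69.4% |
| 5% | 47.5% v 23.7% | 23.7 | 65.7% |
| 10% | 45% v 22.5% | 22.5 | 62.0% |
| 20% | 40% v 20% | 20.0 | 54.5% |

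**The case against.** The case against is substantial, and much of it stands.

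- **The entry rule is a coherent choice.** Activity is defined by a cited composite score that is also a primary outcome. That stands for the primary analysis. It does not help ACR, because the clash arises between two rules that the article states in full: entry and the joint component of ACR.
- **The primary analysis is unaffected in kind.** DAS28-CRP and CDAI changes are computable at a zero count, and the sample size rests on DAS28-CRP. A reader might infer that the primary comparison is biased. It is not: any share of such patients is equal in expectation between arms.
- **It is tempting to say that anyone with a zero 28-joint count can never be an ACR responder.** The article writes TJC28 and SJC28 in the DAS28-CRP formula but plain TJC and SJC for ACR. If ACR uses a wider joint set, zero on 28 joints need not be zero for ACR. Entry still guarantees no non-zero count on either set.
- **Handling of a zero baseline may be settled in a document not shown.** That is fair, and its absence here is no fault. The (1−f) factor holds only if such patients count as non-responders. If they are left out, the rates are not diluted but the number analysed falls.
- **The affected share is unknown.** Nothing in the documents supports a share of 10% or 20%, and it could be negligible.
- **A reader might lean on fibromyalgia.** The Introduction says "More frequent comorbidities in female RA, such as depression, osteoporosis and fibromyalgia, also may impact treatment choice and outcomes", which is a statement about relative frequency and gives no rate for this trial. Exclusion criterion 4 bars other rheumatic diseases through an open list that may or may not cover fibromyalgia.
- **A reader might also say that the trial misses the synovitis which KBXG is meant to treat.** US7 scores synovitis by ultrasound independently of clinical swelling, and the aims extend to symptoms and disease activity in general.

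**Conclusion.** The concern holds in a limited form. The stated entry rule admits patients with no swollen joint at ordinary values of the other components and, less readily, patients with no tender joint. For any whose baseline count is zero on the joint set used for ACR, the stated ACR condition is impossible to meet or undefined.

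The consequence is a loss of sensitivity in one secondary outcome, by the factor (1−f) on the rates and their difference if these patients count as non-responders. Its size cannot be fixed from the documents because f is not given. The conclusion rests on the assumed units for CRP and VAS and on entry DAS28 being the CRP version. It is worth correcting because the correction is cheap, not because the trial's main result is at risk.

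**What to change.** Add to inclusion criterion 2 a requirement for at least one tender and at least one swollen joint at baseline, checked before allocation and counted on the joint set used for ACR. State which joint set that is.

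For patients already enrolled, keep the ACR analysis in the full intention-to-treat set and add one restricted to those with baseline TJC ≥ 1 and SJC ≥ 1. The restriction uses baseline values only, so the comparison within it remains randomised. The number analysed will be smaller by an amount not yet known.

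**Cost.** One line of text. Joint counts are already needed for DAS28-CRP at the enrolment visit in Table 2; a wider ACR set would have to be counted then too. Expect a few more screen failures and a slightly narrower population at a single centre.

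This floor removes undefined responses but does not separate ACR20, ACR50 and ACR70 at a count of 1. A higher floor would help there, at the price of slower recruitment and a narrower population. That is an optional trade-off for the trial team.

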##### Diagnostic criteria for TCM syndrome differentiation

Patients have at least two of the primary symptoms, or one of the primary symptoms and more than two of the secondary symptoms, indispensable tongue and pulse listed in the following to be diagnosed with the Qi-blood deficiency, toxin-heat blocking joints syndrome.1). Primary signs and symptoms: joint pain; joint swelling; morning stiffness; activity limitation.2). Secondary signs and symptoms: redness of joint; local joint fever; fatigue; thirsty upset; dry stools and yellow urine.3). Tongue and pulse: red tongue with yellow greasy or thin yellow fur, rapid and slippery pulse or soft pulse.

#### Inclusion criteria

Participants meeting the following criteria will be included:1) Females aged 18–65 years old.2) Patients who meet the diagnostic criteria for RA, meet the diagnostic criteria for active RA, and meet the Qi-blood deficiency, toxin-heat blocking joints syndrome.3) A duration of RA for at least 3 months prior to enrollment.4) Patients who take only one kind of csDMARDs (methotrexate at a dose of 15–20 mg per week at least or leflunomide at a dose of 20 mg per day) were given a stable dose for at least 12 weeks before screening and remained at the same dose for the rest of the treatment.5) Patients who volunteer to participate in the trial and sign the informed consent form.

#### Exclusion criteria

Participants with any of the following criteria will be excluded:1) Patients who are pregnant, lactating, or plan to become pregnant.2) Patients with serious primary diseases involving in cardiovascular, liver, kidney, brain, endocrine and hematopoietic system, and psychiatric disorders.3) Patients with severe chronic infection and carcinoma.4) Patients with other rheumatic diseases including but not limited to myositis, systemic lupus erythematosus and sjogren’s syndrome.5) Patients who are allergic or sensitized to the test drugs.6) Patients who have changed their dose within 2 weeks of screening or have newly taken NSAIDs within 4 weeks of screening.7) Patients who have received oral corticosteroids of more 10 mg per day, have newly taken within 4 weeks, or have changed their dose within 2 weeks of screening.8) Patients who have received bDMARDs or received two or more csDMARDs before screening.

### Interventions

Patients in the experimental group will receive KBXG. Patients in the control group will receive placebo granules as the comparator. Two groups will continue their original treatment regimen during the trial. Both Kunbixiao granules and placebo granules will be provided by the Chinese Medicine Preparation Department, Xiyuan Hospital of China Academy of Chinese Medical Sciences. According to the quality control analysis, the quality of KBXG should meet the Chinese Medicine Standards of the State Food and Drug Administration. The herbal components of kunbixiao are shown in Table 1. Placebo granules are composed of 95% maltodextrin and 5% KBXG to achieve an odor, color, taste, and texture comparable to KBXG. The details are presented in the Supplementary Material S2. KBXG or placebo granules will be taken orally twice daily dissolving in warm water for 12 weeks. The methods and results on the quality control of KBXG and placebo granules are available in the Supplementary Material S3.

**TABLE 1 T1:** The components of the Chinese herbal formula Kunbixiao.

Herbal name	Dosage(g)	Produced from
*Lonicera japonica* Thunb. [Caprifoliaceae]	30	Dried flower bud
Rehmannia glutinosa (Gaertn.) DC. [Orobanchaceae]	30	Dried root
Scrophularia ningpoensis Hemsl. [Scrophulariaceae]	20	Dried root
Paeonia lactiflora Pall. [Paeoniaceae]	15	Dried root
Cremastra appendiculata (D.Don) Makino [Orchidaceae]	10	Dried pseudobulb
Angelica sinensis (Oliv.) Diels [Apiaceae]	20	Dried root
Conioselinum anthriscoides ‘Chuanxiong’ [Apiaceae]	10	Dried rhizome
Codonopsis pilosula (Franch.) Nannf. [Campanulaceae]	30	Dried root
*Glycyrrhiza* glabra L. [Fabaceae]	10	Dried root and rhizome
Microsorum scolopendria (Burm.f.) Copel. [Polypodiaceae]	3	Dried body
Sinomenium acutum (Thunb.) Rehder & E.H.Wilson [Menispermaceae]	15	Dried rattan
Pyrola calliantha Andres [Ericaceae]	15	Dried herba

Participants are required to return both the opened and unopened drug and package. Counseling will be provided by rheumatologist about management in RA. Participants will be considered as dropouts if they fail to complete the study for various reasons or use prohibited drugs.

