#### Prohibited

It includes medicines that can affect the primary outcome, such as 1) Chinese medicine with the same or similar function as KBXG, 2) corticosteroid injections, 3) Oral corticosteroid/NSAIDs administered for other diseases, and 4) bDMARDs, cell proliferation inhibitors, and/or immunosuppressants.

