### Statistical methods

Data analysis will be completed using SPSS 23.0, according to the intention-to-treat analysis and the per-protocol analysis. Baseline analyses will be performed using analysis of variance or non-parametric tests for continuous variables, and chi-squared or Fisher’s exact tests for categorical variables, respectively. Changes from baseline to post-treatment in DAS28-CRP, CDAI, TCM syndrome scores, VAS, average hands grip strength, HADS, L-BDM and US7 will be analyzed. The results of the two groups will be analyzed using analysis of covariance with associated 95% confidence intervals. The rates of participants achieving good responses on ACR will be compared. A two-sided *p* value of < or = 0.05 is considered statistically significant. Multiple imputations will be used to handle any missing data. For safety, the incidence of AEs will be analyzed and compared. The details of each AEs will be analyzed.

Participants with poor adherence, compliance of experimental drug <80%, or those no longer receiving medication and undergoing testing during the study will be included in the intention-to-treat analysis and excluded from the per-protocol analysis. Multiple imputation will be used for missing data.

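### Classing every user of a prohibited drug as a dropout invites avoidable loss of primary-outcome data

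*Protocol article*

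**What the plan says.** The dropout rule stands at the end of the Interventions section: "Participants will be considered as dropouts if they fail to complete the study for various reasons or use prohibited drugs". Either condition alone is enough, and there is no exception for a participant who remains available for assessment.

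The Prohibited section, under Concomitant medications, describes the drugs by purpose and by example: "It includes medicines that can affect the primary outcome, such as". Four items follow: Chinese medicine with a function like that of KBXG; corticosteroid injections; "Oral corticosteroid/NSAIDs administered for other diseases"; and bDMARDs, cell proliferation inhibitors or immunosuppressants.

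The Statistical methods section plans ITT and per-protocol analyses and sets a rule for certain departures, which it lists as follows: "Participants with poor adherence, compliance of experimental drug <80%, or those no longer receiving medication and undergoing testing during the study". On how the analyses treat these women, the section says that they "will be included in the intention-to-treat analysis and excluded from the per-protocol analysis". It adds: "Multiple imputation will be used for missing data".

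The Primary outcome section defines what would be lost: "The primary outcomes are the change in DAS28-CRP and CDAI at every visit". The Trial design section sets the post-baseline visits at weeks 4, 8, 12 and 24.

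**The concern.** The dropout rule merges two different things. Non-completion means that the patient can no longer be measured. Taking a prohibited drug is an event in a patient who may still come to every visit. Under one label, the natural response at a site is to treat both alike and end follow-up.

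Two features make this more than a matter of vocabulary. First, the protocol itself describes these drugs as able to influence the primary outcome. Some of them, such as a corticosteroid injection or a bDMARD, could be given because the RA has worsened. Values missing after such use need not be a random subset, and imputing them from women who did not take the drugs may misstate them, in a direction that cannot be known in advance. Second, the loss would arise after randomisation and would be self-inflicted. Whether visits continue is an instruction for trial conduct, and no analysis plan can recover values that were never collected.

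**Working it through.** **1. The only stated figure that touches dropout.** Inputs from the Sample size section: 68 participants needed, 20% loss allowance, 90 planned.

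- 68 / (1 − 0.20) = 85, which matches the stated minimum.
- 90 − 68 = 22 losses (22/90 = 24.4%) before the number falls below 68.

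The allowance is applied correctly, so nothing here shows a shortfall caused by the dropout rule.

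**2. The rules side by side.**

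| Event after randomisation | Called a dropout (Interventions) | Stays in ITT, leaves per-protocol (Statistical methods) |
|---|---|---|
| Does not finish the trial | yes | yes, where medication has stopped |
| Poor adherence or compliance below 80% | not on this ground alone | yes |
| Uses a prohibited drug | yes | not named |

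The third row is the gap. The one rule that mentions prohibited-drug use gives it the label of a lost patient, and the rule that would place such a patient in the analysis sets does not name her. The phrase about medication and testing in the latter rule can be read as both having stopped, or as testing going on after medication has stopped. On either reading those women stay in ITT.

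**3. Values at risk per labelled woman, if measurement stops.** Inputs: 4 post-baseline visits. The Primary outcome section gives 4 DAS28-CRP + 4 CDAI = 8 values. Table 2 marks CDAI only to week 12, which gives 4 + 3 = 7.

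| Labelled after the visit at | Lost, by the Primary outcome section | Lost, by Table 2 |
|---|---|---|
| week 4 | 3 + 3 = 6 of 8 (75%) | 3 + 2 = 5 of 7 (71%) |
| week 8 | 2 + 2 = 4 of 8 (50%) | 2 + 1 = 3 of 7 (43%) |

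If measurement continues, the count is 0 in every cell.

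**4. How many women.** The article gives no rate of prohibited-drug use. As an assumption only, 5% to 20% of an arm of 45 would be 45 × 0.05 = 2.25 to 45 × 0.20 = 9, or about 2 to 9 women. The documents do not support any estimate of the error per imputed value, so no shift in the treatment effect is calculated.

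**The case against.** The strongest reply is that the harm needs a step that the article never takes. No sentence ends visits after prohibited-drug use, and none sets an observed value to missing. Imputation is reserved for missing data, and an observed value is not missing. A status label in one section and analysis sets in another do not contradict each other. All of this stands. A reader might infer that users of prohibited drugs are removed from ITT, or that their recorded values will be thrown away. The documents do not support either inference: ITT is planned, and even women who have stopped medication are kept in it.

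A second reply is that a condensed article leaves such detail to the full protocol or the analysis plan. That would answer a complaint about silence. It does not answer a rule that is printed here and worded so that it invites the wrong conduct.

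A third is that values after a confounding drug are not obviously the right ones to analyse, and that imputing them under a hypothetical strategy is a recognised choice. That is fair, but it does not argue for ceasing to measure. Collected values can be set aside in an analysis that calls for it, so continued measurement serves any estimand.

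Finally, the ban can be read narrowly. The lead-in limits it to drugs able to influence the primary outcome, so a short NSAID course for an unrelated complaint is caught only on the strictest reading. That stands too, and it means the number affected could be small.

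**Conclusion.** The point holds as a minor one, best described as a cheap improvement. The dropout definition puts measurable women in one class with lost ones, and the rule for analysis sets does not correct this because it leaves prohibited-drug use out.

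The size is conditional. It is nil if sites go on measuring, and it is most of a woman's remaining primary-outcome data if they stop early in treatment. The conclusion assumes only that some staff would give the word dropout its usual meaning. It does not rest on any assumed frequency of use or size of imputation error. A reader might go further and infer a power problem or a biased primary result. The article does not support that: its loss allowance is computed correctly, and it gives no rate of use from which to work out a bias.

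**What to change.** In the Interventions section, define a dropout by failure to complete the trial alone. State that use of any drug on the Prohibited list after randomisation is recorded as a protocol deviation, that the scheduled visits continue to week 24, and that the observed DAS28-CRP and CDAI values are analysed in ITT. In the Statistical methods section, add prohibited-drug use to the reasons for leaving the per-protocol set.

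The cost is a wording amendment, since the visits are already scheduled and both analyses already planned. The downside is that a few women with a confounding exposure stay in ITT. The per-protocol analysis is only a partial check on their influence, because it also removes women with poor adherence and so cannot isolate the effect of prohibited-drug use. No change to the eligibility criteria or to the permitted medications is needed.
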